**10.3 Statistical Analyses**

Statistical analyses for the two primary hypotheses will follow the intention-to-treat paradigm, which means that all randomized patients with baseline and 16 week liver enzyme, OGTT, HbA1c,lipid profile and 1H MRS hepatic fat content will be included in the treatment group to which they were assigned. Missing values will remain missing and patients will be censored at their last follow‐up assessment.

The chi-square test and analysis of covariance or Kruskal-Wallis H test were used to compare baseline variables among the groups for categorical and continuous variables, respectively. Comparisons of the continuous measures before and after treatment were made with the use of a paired t-test, and the differences from baseline to 16 weeks in BBR plus lifestyle intervention group or pioglitazone plus lifestyle intervention group were compared with the lifestyle intervention group using the analysis of co-variance model respectively, in order to adjust for baseline value. Given the fact that there were two planned primary comparisons, bonferroni-adjusted P values of less than 0.025 were considered to indicate statistical significance.

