**1.2 Schedule of Activities and Assessments**

| Assessment/procedure | **screening（V0）** | **Weeks from randomization** | | | | |
| --- | --- | --- | --- | --- | --- | --- |
|  |  | **V1** | **V2** | **V3** | **V4** | **V5** |
|  | **-4 week** | **0 week** | **4 week** | **8 week** | **12week** | **16week** |
| Consent | ● |  |  |  |  |  |
| Screening questionnaire | ● |  |  |  |  |  |
| Baseline medical history | ● |  |  |  |  |  |
| Follow up medical history | ● | ● | ● | ● | ● | ● |
| Inclusion/exclusion criteria | ● | ● |  |  |  |  |
| Randomization |  | ● |  |  |  |  |
| Health education & diet guide |  | ● | ● | ● | ● | ● |
| Review of concomitant drugs |  |  | ● | ● | ● | ● |
| Review for adverse effects |  |  | ● | ● | ● | ● |
| Drug dispensing |  | ● | ● | ● | ● |  |
| Review of drug adherence |  |  | ● | ● | ● | ● |
| Nutrition questionnaire |  | ● |  |  |  | ● |
| Activity questionnaire |  | ● |  |  |  | ● |
| Physical exam (Detailed/Focused) | D | F | F | F | F | D |
| OGTT with insulin |  | ● |  |  |  | ● |
| Fasting glucose/2h after meal | ● |  | ● | ● | ● |  |
| Fasting lipid profile | ● | ● |  |  |  | ● |
| Liver and renal fuction | ● | ● | ● | ● | ● | ● |
| Blood and urine routine |  | ● | ● | ● | ● | ● |
| HbA1c | ● |  |  |  |  | ● |
| Pregnancy test (females) |  | ● |  |  |  | ● |
| Serum, plasma for banking | ● | ● | ● | ● | ● | ● |
| Hepatic virus anti-body（HBsAb、HCV-Ab） | ● |  |  |  |  |  |
| ECG | ● |  |  |  |  | ● |
| Liver fat content（MRS） | ● | ● |  |  |  | ● |

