**4.3 Outcomes**

The primary outcomes are the changes in OGTT (glucose, insulin, AUC of glucose), HbA1c; lipid profile（TC, TG, HDL-c, LDL-c, ApoA, ApoB, ApoE, Lpa); liver enzymes (ALT, AST, γ-GT, ALP). The secondary outcome is liver fat content by 1H NMR spectroscopy.

Safety endpoint includes serious adverse events and non-serous adverse events. Adverse event collection was conducted at each visit after baseline. No specific laboratory safety tests are required during this study. However, if a laboratory abnormality is clinically relevant or leads to an adverse event report, specific appropriate actions may be required. ECG will be performed at the beginning and end of the study.

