**9.3 Visit 2 (V2): 4 weeks after randomization**

Evaluation will include patient concomitant diseases and Concomitant medications, diet and exercise diary. A physical examination will be performed, including measurement of weight (kg) , waist and hip circumference, and vital signs (supine systolic and diastolic blood pressure, heart rate)Laboratory tests will be performed (liver and renal function, OGTT blood glucose + insulin, blood and urine routine).

participants receive standardized recommendations concerning life-style modification (dietary modification, weight loss, exercise).

Compliance will be assessed by counting returned tablets using the equation as the follows:

Compliance=(dispensed drug tablets- returned drug tablets) /planned drug tablets

The compliance should be been 80%-120%.

All adverse events will be managed and reported in compliance with all applicable regulations.

The investigator should dispense the specific drugs determined at randomization to eligible participants at each visit.

An appointment will be made for next study visit (8 weeks after randomization).

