**10.2 Sample Size Estimation**

The planned sample size for the trial was 180 patients with equal allocation to each of the three treatment groups (60 per group). The sample size estimates were based upon a two-group, binomial comparison of the proportions of patients satisfying the decrease in liver fat content over the course of treatment either with pioglitazone or berberine. Since our current study had three treatment groups and two primary hypotheses, the assumption was made that the two primary comparisons, pioglitazone vs. no-drug control and berberine vs. no-drug control, required the type I error estimate be reduced from 0.05 to 0.016 in accordance with three-group comparison. Expected proportions improved were speculated using pilot data from pioglitazone-treat NAFLD studies. There were no available data at the time of study design to estimate liver steatosis response with berberine, which was assumed, for purposes of planning the trial, to be the same as for pioglitazone.

The sample size calculations were performed using the formula: n1=n2=2[(tα+ t2β)s/δ]^2^ with a standard deviation of NAFLD patients liver fat content (s=6.87%, from our prior study), with an expected difference in proportion of improvement between pioglitazone or berberine group and the control group (δ=0.05), with an α level of two-sided type I error (0.016, corrected for three-group comparison), and with a β level of type II error (0.10; i.e., 90% power). The number per group, using the above assumptions was 52. Inflating this number by the 15% expected missing data rate yielded approximately 60 patients per group, or a total of 180 for the trial.

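### Liver enzymes are scheduled at weeks 4, 8 and 12, but the efficacy analysis in Protocol 10.3 uses only baseline and week 16, and the synopsis handles a missing week-16 value differently: a modest loss, cheaply repaired

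*Protocol*

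**What the plan says.** - **Outcomes.** Protocol 4.3 lists the primary outcomes as changes in OGTT (three measures), HbA1c, the lipid profile (eight measures) and "liver enzymes (ALT, AST, γ-GT, ALP). The secondary outcome is liver fat content by 1H NMR spectroscopy".
- **Schedule.** In Protocol 1.2 the row "Liver and renal fuction" is ticked at every visit from V0 to V5. The text for V2 lists "liver and renal function, OGTT blood glucose + insulin, blood and urine routine", and 9.4 and 9.5 list the same tests for V3 and V4. The panel is not itemised at these visits. That it covers ALT, AST, γ-GT and ALP is a reasonable inference, since those enzymes are the primary liver measures.
- **Model.** Protocol 10.3 says that "the differences from baseline to 16 weeks in BBR plus lifestyle intervention group or pioglitazone plus lifestyle intervention group were compared" with the lifestyle arm, "using the analysis of co-variance model respectively, in order to adjust for baseline value". The synopsis states the same model.
- **Analysis set.** In 10.3, "all randomized patients with baseline and 16 week liver enzyme, OGTT, HbA1c,lipid profile and 1H MRS hepatic fat content will be included". The synopsis has the same definition.
- **Missing data.** 10.3 leaves missing values missing and says patients are censored at their last assessment. The synopsis says a patient without the required data is treated as unimproved and compared in the assigned group.
- **Expected missingness.** Protocol 10.2: "Inflating this number by the 15% expected missing data rate" takes 52 per group to about 60.

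**The concern.** A change score needs only its two end points while nobody is missing. The protocol expects 15% missing, so the interim enzyme values carry information about patients whose week-16 value is absent. The analysis in 10.3 does not use it.

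Two things are at stake for the four enzymes. One is precision, because part of what is lost with a missing week-16 sample could be recovered from weeks 4–12. The other is bias. The trial is open and has a no-drug arm, and liver results accumulate at each visit. If leaving depended on those results, and did so differently by arm, a comparison of patients with week-16 data would be shifted. A model that includes the interim values allows for that dependence.

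The two missing-data rules add to the problem. The same patient is absent under 10.3 and unimproved under the synopsis. Neither rule works for an ANCOVA: censoring does not apply to it, and unimproved is not a value of a continuous change.

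**Working it through.** **1. Share of the primary measures.** OGTT 3 + HbA1c 1 + lipids 8 + enzymes 4 = 16, so the enzymes are 4 of 16.

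**2. The plan's own figure.** Inputs from 10.2: s = 6.87, δ = 5 percentage points, two-sided α = 0.016, power 90%.
n = 2[(2.409 + 1.282) × 6.87/5]² = 51.42, rounded up to 52. This reproduces. Then 52 × 1.15 = 59.8, or 60 per group. The calculation concerns liver fat, a secondary outcome, so it gives no planned power for enzymes.

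**3. Patients lost from the 10.3 analysis.** If the 15% applies to enzymes, 0.15 × 60 = 9 per arm lack week 16 and 51 remain.

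**4. What the interim values recover.** The protocol gives no enzyme correlation or dropout timing, so both are assumptions. Let R² be the share of baseline-adjusted week-16 variance explained by weeks 4–12. If all nine leave after week 12, the variance of the adjusted week-16 mean is proportional to

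(1 − R²)/51 + R²/60.

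Example with a constant correlation of 0.7:
- Correlation between visits given baseline: (0.7 − 0.49)/(1 − 0.49) = 0.412.
- R² = 3 × 0.412²/(1 + 2 × 0.412) = 0.279.
- Variance factor: 0.721/51 + 0.279/60 = 0.01879.
- Effective n = 1/0.01879 = 53.2, against 51 (+4.4%).

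The same information calculation over correlations 0.5–0.9, constant or decaying with time:

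| When the nine leave | Effective n per arm | Gain over 51 | Power, if 80% at n = 51 (α 0.025) |
|---|---|---|---|
| Last visit spread evenly over weeks 0–12 | 51.7–53.7 | 1–5% | 80.6–82.2% |
| All after week 12 | 52.6–56.7 | 3–11% | 81.3–84.3% |

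With evenly spread dropout this recovers about 1 to 3 of the 9 patients per arm. With nothing missing, effective n is 60 either way and there is no gain.

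**5. Bias, as an illustration.** Simulation with 60 per arm, about 15% monotone missing and correlation 0.5–0.8. Controls are assumed to leave more often after a high enzyme value, while drug-arm dropout is random. The week-16-only ANCOVA is then biased by about 0.02–0.06 SD, or 0.2–0.3 standard errors (SE). The repeated-measures estimate shows essentially none.

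What a shift of that size does at two-sided 0.025 (critical value 2.241; 80% power corresponds to a mean of 2.241 + 0.842 = 3.083):
- Against the drug: Φ(0.842 − 0.2) = 74% and Φ(0.842 − 0.3) = 71% power.
- In its favour, with no true effect: Φ(−2.241 + 0.2) + Φ(−2.241 − 0.2) = 0.028 for 0.2 SE, and 0.032 for 0.3 SE.

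**The case against.** The strongest reply is that a baseline-adjusted ANCOVA at week 16 is a standard, valid analysis of a 16-week change, and that Protocol 10.1 calls section 10 an overview and leaves details to an SAP. The first part stands: the method is not wrong in itself. The second does not dispose of the point, because 10.3 names the model, time points, analysis set and significance level. What is questioned is a stated choice, although an SAP could add a repeated-measures or sensitivity analysis.

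A reader might infer more than the protocol supports:

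- **That the interim data are discarded.** They are unused only in the stated efficacy analysis. Protocol 3.2 makes laboratory changes a safety outcome, and the safety monitoring section requires quarterly counts of patients with hepatic toxicity.
- **That early leavers contribute nothing.** This is true of 10.3 read alone. The synopsis counts them as unimproved, and 7.5.3 keeps patients who stop drug in follow-up to scheduled completion, so stopping drug need not mean losing week 16.
- **That enzymes will be 15% missing.** That rate belongs to a sample size built on liver fat.
- **That the ANCOVA is biased.** Nothing in the protocol indicates enzyme-driven leaving. The simulated mechanism is assumed, and the repeated-measures estimate is unbiased there because dropout was made to depend only on observed values. Dropout for unobserved reasons could bias both analyses.

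**Conclusion.** The point holds in a limited form. For four of the sixteen primary measures, the stated efficacy analysis leaves three scheduled on-treatment values unused, and 10.3 and the synopsis disagree on what happens to a patient without week 16. The precision at stake is about 1–5% in effective sample size. That rests on 15% missing, evenly spread dropout and correlations of 0.5–0.9; 11% needs every leaver to go after week 12 with very high correlation. The bias of 0.02–0.06 SD shows what differential, result-driven leaving could do. It is not a prediction for this trial.

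The change is worth making because it is cheap and its missing-data assumption is weaker than that of the completers analysis. The trial's validity does not hinge on it.

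One related conflict affects the scope. The V2–V4 texts list OGTT glucose and insulin, while the schedule ticks "OGTT with insulin" only at weeks 0 and 16. These passages must be reconciled. If the visit texts stand, the same point extends to the OGTT measures.

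**What to change.** In 10.3 and the synopsis:

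1. For ALT, AST, γ-GT and ALP, state a mixed model for repeated measures on the V2–V5 values, with arm by visit, baseline by visit and unstructured covariance. Keep the week-16 contrast of each drug with control, at 0.025, as the primary estimate.
2. Define the set for this analysis as all randomised patients with a baseline and at least one post-baseline value.
3. Replace both missing-data sentences (censored at last assessment; considered unimproved) with one rule that fits this model.
4. Keep ANCOVA for measures taken only at baseline and week 16.
5. State that the interim liver panel includes the four enzymes, if it does.

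The cost is a few sentences and a little programming, with no new visits or samples. The downsides are reliance on a missing-at-random assumption, and a different model and population for 4 of the 16 measures.

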**4. Study design and management overview**

**4.1 Study Design Overview**

The study is a three-centers, randomized, open, controlled clinical trial of treatment with pioglitazone, berberine or no drug on the basis of life style intervention for NAFLD patients with IGR or T2DM. The screening period for evaluating eligibility and collecting baseline data lasted up to 4 weeks before randomization. Eligible patients were randomized to receive pioglitazone (15 mg q.d), berberine (0.5g t.i.d.) or no-drug on basis of Life style intervention for 16 weeks. The primary comparison will be made using an intention-to-treat analysis of the change in OGTT (glucose, insulin, AUC of glucose), HbA1c; lipid profile（TC, TG, HDL-c, LDL-c, ApoA, ApoB, ApoE, Lpa); liver enzymes (ALT, AST, γ-GT, ALP). The secondary outcome is liver fat content by 1H NMR spectroscopy.

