**9 Study Procedures**

**9.1 Screening (V0): 4 weeks before randomization**

A screening form will be completed for all patients in whom enrollment is considered. The patient will receive complete information about the study, both orally and in writing. Consent will be obtained directly from the subject prior to enrollment. Baseline evaluation will include patient demographic information, medications, past medical history, family history, cigarette and alcohol use, examination findings. A physical examination will be performed, including measurement of weight (kg), waist and hip circumference, and vital signs (supine systolic and diastolic blood pressure, heart rate). Laboratory tests will be performed (liver and renal function, OGTT blood glucose, HbA1c, HbsAg, HCV-Ab, electrocardiogram and hepatic fat content by 1H MRS).

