**9.2 Visit 1 (V1)**

Evaluation before randomization will include patient demographic information, medications, diet and exercise information, past medical history, family history, cigarette and alcohol use, and physical examination. Laboratory tests will be performed (liver and renal function, OGTT blood glucose + insulin, HbA1c, lipid profile, blood and urine routine, urine pregnancy test and hepatic fat content by 1H MRS).

The statistician will develop a master randomization list, with stratification blocked to assure an equal distribution of treatments at each participating site. A study number will correspond to a specific medication packet. This identifying number will be coded on the enrollment confirmation.

The patient will receive 4-week study medication and be instructed how to take the study medication. Time of first study drug administration will be recorded. Study drug will be started the next day after randomization. participants receive standardized recommendations concerning life-style modification (dietary modification, weight loss, exercise).

 An appointment will be made for next study visit (4 weeks after randomization).

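### Liver fat, liver enzymes and (per the schedule) lipids are measured at both V0 and V1, but the ANCOVA adjusts for one baseline value with no visit named; taking change from V1 and adding V0 as a second covariate would use both

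*Protocol*

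**What the plan says.** Section 10.3 compares the change from baseline to week 16 in each drug arm with control: it is "compared with the lifestyle intervention group using the analysis of co-variance model respectively, in order to adjust for baseline value". The synopsis describes the same model. Both also plan a paired t-test of before against after treatment. No visit is named as baseline.

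The schedule in section 1.2 marks three rows at both V0 and V1: "Liver fat content（MRS", "Fasting lipid profile" and "Liver and renal fuction". Sections 9.1 and 9.2 also list MRS and liver function at both visits, but they list lipids at V1 only.

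The labels differ by place. Section 4.1 states: "The screening period for evaluating eligibility and collecting baseline data lasted up to 4 weeks before randomization". The synopsis and section 1.1 say the same. Section 9.1 opens its list for V0 with "Baseline evaluation will include patient demographic information", whereas section 9.2 describes V1 as "Evaluation before randomization will include patient demographic information, medications, diet and exercise information" and does not use the word baseline. Section 4.3 has adverse events collected at the visits that follow baseline, and the schedule starts that review at V2. This implies that baseline there is V1.

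**The concern.** The duplicated measures are the four liver enzymes, the eight lipids (on the schedule alone) and liver fat. That is 12 of the 16 primary variables plus the secondary outcome on which the sample size rests. For each of them the stated wording can be met with V0 or V1.

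Two things are at stake. First, a model with one baseline covariate leaves out a second pre-randomisation measurement of the same variable, which would normally help to predict week 16. Second, the within-arm before/after change differs with the value used. A V0 baseline stretches a 16-week change to as much as 20 weeks, part of it before treatment. If entry was decided on V0, it also carries more regression to the mean. The term also enters two other rules: the analysis set requires baseline and week-16 data, and the interim analysis is triggered by completed baseline and week-16 MRS examinations.

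**Working it through.** **The plan's own figure.** Section 10.2 gives s = 6.87, δ = 5 points (0.05 as printed), two-sided α = 0.016 and 90% power. Then n = 2[(2.409 + 1.282) × 6.87 / 5]² = 51.42, rounded up to 52 per group, as stated. Inflated, 52 × 1.15 = 59.8, or 60. This calculation takes no credit for baseline adjustment.

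**Precision.** Let ρ be the correlation of a single baseline value with week 16, and r the correlation of V0 with V1. Neither is in the protocol, so both are assumed. V0 and V1 are taken as equally correlated with week 16. Relative to the unadjusted variance, the residual variance is:

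- one baseline covariate: 1 − ρ²
- both values: 1 − 2ρ²/(1 + r)

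Reduction in residual variance from using both values instead of one:

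| ρ | r = 0.7 | r = 0.8 | r = 0.9 | r = 0.95 |
|---|---|---|---|---|
| 0.4 | 3.4% | 2.1% | 1.0% | 0.5% |
| 0.5 | 5.9% | 3.7% | 1.8% | 0.9% |
| 0.6 | 9.9% | 6.2% | 3.0% | 1.4% |
| 0.7 | 17.0% | 10.7% | 5.1% | 2.5% |

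Middle case, ρ = 0.6 and r = 0.9: 1 − 0.36 = 0.640 against 1 − 0.72/1.9 = 0.621. Applied to 51.42, these give 33 and 32 patients per group. The 17% corner needs week 16 to track baseline as closely as V0 tracks V1, which is optimistic with diet, exercise and drug in between.

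The extra covariate costs one degree of freedom. With 104 to 120 patients in a two-arm comparison (2 × 52 to 2 × 60), that is about 1%. In three of the 16 cells (1.0%, 0.9% and 0.5%) the gain therefore does not exceed the cost; in the other 13 it does.

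**Bias of the randomised contrast.** A simulation assumed mean 20%, SD 6.87, entry on V0 ≥ 13%, a true effect of −5, 52 per arm and 2,000 runs. The ANCOVA estimate was about −5.0 with V0, with V1 or with their mean. At r = 0.8 and ρ = 0.7 the standard errors were 0.980, 0.973 and 0.928.

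**Within-arm change.** The same simulation gave these mean changes in the control arm, where no real change was built in:

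| r | ρ | from V0 | from V1 | gap |
|---|---|---|---|---|
| 0.8 | 0.5 | −0.93 | −0.57 | 0.36 |
| 0.8 | 0.7 | −0.57 | −0.19 | 0.38 |
| 0.9 | 0.5 | −0.95 | −0.76 | 0.19 |
| 0.9 | 0.7 | −0.55 | −0.36 | 0.19 |

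The gap is about 0.2 to 0.4 points of liver fat, and V1 is not free of regression to the mean either. These figures assume selection on V0 alone. If the same threshold is applied at both visits, the expected V0 − V1 gap is zero by symmetry.

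**Which value is subtracted.** When V0 and V1 are both covariates, change from V0 and change from V1 differ only by a linear combination of covariates. The estimated arm difference and its standard error are then identical. The two-covariate model therefore removes the ambiguity from the between-arm comparison.

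**Schedule against text before randomisation:**

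| Measure | Section 1.2 | Sections 9.1 and 9.2 |
|---|---|---|
| Lipids | V0, V1 | V1 only |
| HbA1c | V0 only | V0, V1 |
| OGTT glucose | V1 only (V0: fasting and 2 h after a meal) | V0, V1 |

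If the schedule governs, HbA1c has no V1 value. If the text governs, HbA1c and OGTT glucose are duplicated and lipids are not.

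**The case against.** The strongest reply is that naming the baseline visit and listing covariates is ordinary SAP work. Section 10.1 calls section 10 an overview and defers to a SAP that is not at hand. That stands: the missing visit is not an error by itself. The deferral protects less than usual, because 10.1 ties the SAP to database lock and code breaking and an open trial has no code to break. A reader might infer that the choice will be made after results are seen, but nothing in the protocol shows that.

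The reply continues that the text already leans to V1. The schedule counts weeks from randomisation with V1 as week 0, so a 16-week change fits V1. The screening period runs up to randomisation, so baseline data collected in it could include V1. In 9.1 the word baseline introduces demographics, history and examination, and the laboratory tests and MRS come in a later sentence. This is fair. It supports choosing V1, but leaves the term used loosely.

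The reply also says that the gain may be small and rests on assumed correlations. That stands too, and it is why a range is given. It does not remove the case for a covariate that is already collected and nearly free.

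**Conclusion.** The point holds as a modest improvement to the model together with a wording inconsistency. Using both pre-randomisation values lowers residual variance by about 0.5% to 17% over the assumed correlations, less about 1% for the degree of freedom. The gain is small when V0 and V1 correlate highly. The within-arm paired change in liver fat moves by about 0.2 to 0.4 points in the simulated cases, if entry is decided on V0.

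Four stronger readings are tempting and are not supported:

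- **That V0 and V1 are both called baseline.** Only screening carries the word; V1 is baseline by implication.
- **That one value is thrown away.** No section says so, and V0 can serve the 13% liver-fat criterion. The stated model simply adjusts for one value.
- **That the primary comparison is biased.** Both values precede randomisation, so the ANCOVA contrast is valid with either. Setting regression to the mean within an arm against the planned 5-point difference between arms would compare unlike quantities.
- **That patients are selected on V0.** The schedule checks inclusion and exclusion criteria at both V0 and V1, and section 5.1 names no visit, so selection on V0 is an assumption.

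**What to change.** In 10.3 and the synopsis, define change from V1 (week 0, the last value before first dose). For liver fat, liver enzymes and lipids, add the V0 value of the same measure as a second covariate in the ANCOVA. Describe V0 as screening in the synopsis and in sections 1.1, 4.1 and 9.1, or state that baseline means V1 wherever the term drives the analysis set and the interim trigger.

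State what happens when V0 or V1 is missing. Section 10.3 leaves missing values missing, so a patient without one covariate would drop out of the two-covariate model. Either accept that loss, or limit that sentence to outcomes and allow a missing covariate to be filled from pre-randomisation data alone.

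Reconcile section 1.2 with 9.1 and 9.2 on which of lipids, HbA1c and OGTT are measured at V0 and at V1. If HbA1c is taken only at V0, name V0 as its baseline. If lipids are taken only at V1, they need no second covariate.

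The cost is wording in the protocol and SAP, a rule for missing covariates, and one degree of freedom per model. It needs no new visit, measurement or patient, provided that the schedule's duplicate measurements are in fact made.

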| **Randomization:** | The statistical group of Public Health College, Fudan University took responsibility for the preparation and administration of randomization plan. Randomization sequence was generated by SAS8 computer software in a three-center, group randomization manner, and the whole procedure was finished by statistical staff who were not engaged in the study. An envelop randomly labeled with drug assignment was issued only if the database showed that the patient was eligible, had signed the consent statement, and had all required baseline data keyed to the database. The randomization scheme assigned patients to join in one group and accept specific treatment. |
| **Primary Endpoint:** | changes in OGTT (glucose, insulin, AUC of glucose), HbA1c; lipid profile（TC, TG, HDL-c, LDL-c, ApoA, ApoB, ApoE, Lpa); liver enzymes (ALT, AST, γ-GT, ALP). |
| **Study Duration for Each**  **Subject:** | Each subject is followed for 16 weeks; the trial will be completed in 3 year |
| **Number of Centers:** | Three clinical centers in China |
| **Sample Size:** | 180 subjects |
| **Primary Statistical Analysis:** | Statistical analyses will follow the intention-to-treat paradigm, which means that all randomized patients with baseline and 16 week liver enzyme, OGTT, HbA1c,lipid profile and MRS hepatic fat content will be included in the treatment group to which they were assigned. Any randomized patient who does not have the requisite data will be considered unimproved on the primary outcome measure and compared by assigned treatment group. Given the fact that there were two planned primary comparisons, bonferroni-adjusted P values of less than 0.025 were considered to indicate statistical significance. Comparisons of the continuous measures before and after treatment were made with a paired t-test, and the differences from baseline to 16 weeks in BBR plus lifestyle intervention group or PGZ plus lifestyle intervention group were compared with the pure lifestyle intervention group using the analysis of co-variance model respectively, in order to adjust for baseline value. |

1. **STUDY FLOWCHARTS**
   1. **Trial Design**

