**10 Statistical Considerations**

**10.1 Statistical Analysis Plans**

This section is an overview of the statistical considerations. Complete details can be found in the Statistical Analysis Plan (SAP). It provides the general specifications for the analysis of the

data to be collected and presented in the Clinical Study Report. A final SAP will be issued prior to database lock and before code breaking. The SAP will define all “pre-specified, planned analyses.”

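### Allocation is stratified by site, but the stated ANCOVA names only the baseline value as covariate; naming centre is a minor, nearly free improvement

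*Protocol*

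**What the plan says.** **Randomisation.** Section 9.2 describes a master list "with stratification blocked to assure an equal distribution of treatments at each participating site". The synopsis is consistent with this: "Randomization sequence was generated by SAS8 computer software in a three-center, group randomization manner". I read the synopsis wording as block randomisation of individual patients within three centres, which is what section 9.2 describes.

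**Analysis.** Section 10.3 compares the baseline-to-week-16 differences in each drug arm with the lifestyle arm "using the analysis of co-variance model respectively, in order to adjust for baseline value". The synopsis repeats the same model. The threshold in both places is the same: "bonferroni-adjusted P values of less than 0.025 were considered to indicate statistical significance". No centre term appears in either description.

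**Where the detail sits.** Section 10.1 calls the chapter an overview and adds: "Complete details can be found in the Statistical Analysis Plan (SAP". That SAP was not available to me.

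**The concern.** Blocking within site keeps the arms nearly equal in size at each centre. Differences between centres therefore largely cancel out of the treatment contrast. A model without centre does not know this. It leaves those differences in the residual variance and reports a standard error larger than the true sampling error of the estimate. Confidence intervals are then too wide, the test runs below its nominal level, and some power is given up. The usual principle is that the analysis should reflect the factors used to restrict the randomisation.

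What is at stake is efficiency and agreement between design and analysis. The trial is open-label, so it also helps to fix the covariates before outcomes by arm are examined.

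**Working it through.** **Inputs from section 10.2:** SD of liver fat content ("s=6.87%, from our prior study"); δ = 0.05, which yields the stated sample size only if read as 5 percentage points of liver fat; two-sided α of 0.016; power 90%; 52 per group before inflation. **From section 10.3:** threshold 0.025 per comparison. **Assumed:** the share ρ of residual variance that lies between centres, since the protocol gives none.

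**Step 1. Reproduce the plan's figure.** In the normal approximation, n = 2[(z₀.₉₉₂ + z₀.₉₀)·s/δ]² = 2[(2.409 + 1.282) × 6.87/5]² = 51.4, so 52 per group. Then 52 × 1.15 = 59.8, or about 60. The stated figures reproduce.

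**Step 2. Effect of leaving centre out.** Hold the total SD at 6.87, with arms balanced within centre and 52 per arm.

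- Reported SE without centre: 6.87 × √(2/52) = 1.347.
- True sampling SE, which the model with centre estimates: 1.347 × √(1−ρ).
- Overstatement: 1/√(1−ρ).
- True level of the nominal 0.025 test without centre: 2[1 − Φ(2.241/√(1−ρ))].
- Power without centre: Φ[(5 − 2.241 × 1.347)/(1.347√(1−ρ))].
- Power with centre: Φ[5/(1.347√(1−ρ)) − 2.241].

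| ρ (assumed) | SE overstated by | True level | Power without centre | Power with centre |
|---|---|---|---|---|
| 0 | 0% | 0.025 | 92.9% | 92.9% |
| 0.01 | 0.5% | 0.024 | 93.0% | 93.2% |
| 0.05 | 2.6% | 0.022 | 93.4% | 94.1% |
| 0.10 | 5.4% | 0.018 | 93.9% | 95.3% |
| 0.20 (stress case) | 11.8% | 0.012 | 95.0% | 97.2% |

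Power without centre also rises with ρ because the total SD is held fixed, so a larger centre share leaves less variance within centres. The cost of omitting centre is the gap between the last two columns: 0, 0.2, 0.7, 1.3 and 2.2 points on the unrounded values.

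**Step 3. Simulation check.** ANCOVA was fitted with and without centre (3 centres, 52 per arm, 20,000 null and 8,000 alternative runs per ρ). The simulated baseline was unrelated to outcome, so 6.87 acts as the residual SD.

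- Mean SE without versus with centre: 1.351 v 1.351 (ρ = 0), 1.351 v 1.316 (0.05), 1.352 v 1.281 (0.10).
- Level without centre: 0.025, 0.020 and 0.019.
- Power without versus with centre: 92.3% v 92.4%, 92.7% v 93.6%, 92.5% v 94.2%.

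Each simulated power has a standard error of about 0.3 points (√(0.93 × 0.07/8000)), so the agreement with step 2 is adequate.

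**Step 4. Sensitivity to α.** At the planning level of 0.016, power without versus with centre is 90.4% v 90.4% (ρ = 0), 90.9% v 91.9% (0.05) and 91.5% v 93.4% (0.10). The loss is slightly larger, at 1.0 and 1.9 points, and power stays above 90% throughout.

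**The case against.** The strongest objection is that a full covariate list belongs in the SAP. Section 10.1 calls the chapter an overview, and adding centre in the SAP would contradict nothing. The phrase about baseline gives the reason for using ANCOVA and does not say that baseline is the only term. A reader might infer that the plan excludes centre; the text does not go that far. What remains is that the protocol is not silent. It describes the model twice and names one covariate, and that description does not match its own allocation scheme. If the SAP includes centre, the protocol should say so too.

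Second, the loss is conditional. A reader might infer that standard errors will be too large and power wasted. That holds only if centres differ in the baseline-adjusted outcome, and with no centre effect the loss is nil. The protocol text reports no scanner or laboratory differences between sites. Section 6 describes standardised lifestyle recommendations, and analysing change with baseline adjustment already removes at least part of any stable centre offset. This objection stands, and it is why the range starts at zero.

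Third, a reader might infer that the trial is underpowered or its test invalid. Neither follows. Type I error falls below nominal, and liver-fat power exceeds 90% either way. That reassurance does not carry over to the primary outcomes (OGTT, HbA1c, lipids, liver enzymes), for which no power can be computed from the document.

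Finally, two separate pairwise ANCOVAs at 0.025 are valid. Fitting one three-arm model is a preference, not a correction.

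**Conclusion.** The point holds as a minor one. The stated model does not reflect the site-stratified randomisation, and the consequence, if there is one, is conservatism. The size given in the brief rests on four assumptions: a centre share of 0% to 10% of residual variance, near-equal arms within each centre, the 0.025 threshold, and 6.87 taken as the residual SD although section 10.2 gives it as the SD of liver fat content. The power figures describe liver fat only, which section 4.3 lists as the secondary outcome. For the primary outcomes the direction of the effect is the same, but its size cannot be derived from the protocol. No conclusion of the trial would be invalidated by the present wording.

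**What to change.** In the synopsis and section 10.3, describe the comparison as ANCOVA of the baseline-to-week-16 change with treatment, baseline value and centre (3 levels) as terms, and use the same wording in the SAP. Settle this before outcomes are examined by arm.

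The cost is one phrase in two places and two degrees of freedom. Centre is known for every patient from the randomisation, so no new data are needed. If centres turn out not to differ, almost nothing is lost: at ρ = 0 the simulated power was 92.3% without centre and 92.4% with it. The sample size does not need to change.
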